### Procedure

All knee injuries from the PTs patient pool are reported to the SC during weekly contact, in which the SC reminds PTs of inclusion criteria and actively seeks information on knee-injured participants in order to approach all potential participants in the patient pool. The number of patients approached and invited (i.e., eligible, ineligible, and declined participation) will be recorded. The SC contacts potential participants that have consented to a pre-screening interview, during which information is provided, inclusion, and exclusion criteria are verified, and, if eligible, the participant is invited to take part in the study. Information provided to potential participants includes only that there is a “mental training intervention” with no details which could be used to replicate the intervention, adhering to Swedish ethical guidelines for participant informed consent. Following pre-screening, the SC has regular contact with participants and physical therapists in order to receive updates on patient progression through rehabilitation. This ensures proper inclusion timing and reduces the risk of late inclusion by reducing dependency on physical therapists with regard to inclusion criteria, as well as ensuring that eligible participants are included in the trial. Rehabilitation during this period is provided according to rehabilitation protocols prescribed at the discretion of the PT until the participant is able to complete single-leg hop tasks, ensuring proper inclusion timing. When the hop ability criterion is confirmed by the PT, written information is provided, and baseline testing takes place, during which the test leader collects informed consent (Additional File 3 – Informed Consent Materials). The intervention then begins, implementing either CaU or MOTIFS training in the clinical setting during treatment. The intervention period is 12 weeks, as studies have shown that physical [28] and psychological [29] factors can be improved in this time span. MOTIFS training accounts for approximately 20 min [30] in a typical 60-min training session. At least 3 supervised or at-home training sessions are performed per week, whereof at least 6 are supervised by a participating PT during the intervention period, resulting in an intervention dose of 36 possible training sessions, with intensity prescribed by the PT. Participants and PTs are made aware of the possibility to end their involvement in the study. Participants may remove themselves at their discretion, or worsening symptoms may require the PT to change treatment strategy. To ensure that participants complete self-report questionnaires, telephone contact may be initiated.

#### Care-as-usual intervention

The control condition includes 12 weeks of “care-as-usual” training (CaU), in which participants receive treatment at the discretion of the participating PT according to commonly used neuromuscular training practices in physical therapy settings in southern Sweden. These typically aim to improve motor control and achieve dynamic stability in people with a knee injury [9]. Emphasis is on the quality and efficiency of movement, with little to no structured psychological training (Additional File 4: Appendix 1.3 [Appendix Table 1 – Care-as-Usual column]).

Participants in the CaU condition are contacted by the SC by telephone three times during the intervention period to ensure adherence to training and provide rehabilitation updates. This is done in order to maintain equal contact as compared with the MOTIFS condition.

##### Motor Imagery to Facilitate Sensorimotor Re-Learning (MOTIFS)

We have developed Motor Imagery to Facilitate Sensorimotor re-learning (MOTIFS), a novel training model designed to integrate psychological training into care-as-usual rehabilitation exercises.

##### Physical background to MOTIFS

The MOTIFS model integrates DMI into care-as-usual neuromuscular training principles. The majority of training is comprised of complex movements with greater speed and intensity in multiple planes at the discretion of the participating PT, for example, hop, change of direction, and pivoting exercises.

##### Psychological background to MOTIFS

An external focus of attention, focusing on something outside the body, may be more beneficial for the development of motor control and movement efficiency than an internal focus on one’s own body and movements [21]. Instructing a person to reach their knees towards a point on the wall during a squat creates an external focus, as opposed to maintaining a knee-over foot position, which is internal. The external focus on specific and experience-based skill practice facilitates automatic processes [21], allowing a PT to help a patient to more easily and correctly execute familiar and relevant movements, such as reaching for a ball in a defensive situation, as opposed to merely reaching towards the wall. Therefore, rehabilitation with integrated functionally equivalent simulations of activity-specific situations may aid in making proper movement patterns more automatic. This, along with implications for motivation [22] and enjoyment and feelings of control [31], indicates that the holistic MOTIFS model may improve psychological and physical rehabilitation outcomes.

##### MOTIFS model principles

MOTIFS training uses principles based on the PETTLEP model of DMI to individualize psychological training based on a person’s own experiences (see Appendix 1.4 for details) [18]. The MOTIFS principles (Table 2; Appendix 1.2) provide clinical guidelines to determine how to physically and psychologically individualize treatment. Following discussions with a patient, the level of complexity of the integrated DMI can be modified (Fig. 2) in order to achieve external and context-specific psychological goals, as well as physical and rehabilitation goals. Shared decision-making is employed to ensure activity-relevant applicability of the PT-prescribed rehabilitation movement in order to increase patient involvement in the design of the exercise itself. This process is repeated throughout rehabilitation to integrate MOTIFS training into CaU exercises, adapting to fit the physical and psychological needs of the individual patient.

**Table 2 Tab2:** Principles utilized in the MOTIFS model

The MOTIFS model modifies Care-as-Usual rehabilitation to create sport-specific exercises individualized to the needs and goals of the patient using as many aspects of PETTLEP motor imagery as possible		
**1**	**Discuss**	A realistic scenario is created through discussion between the PT and patient based on the rehabilitation movement and meaningful and relevant aspects of the participant’s prior experiences
**2**	**Create**	An exercise is created by both the PT and patient which simulates the individualized and realistic scenario
**3**	**Execute**	The activity-specific rehabilitation movement with integrated dynamic motor imagery is executed as realistically as possible, including physical and mental simulation, equipment, and a full-body and context-specific follow-through
**4**	**Evaluate**	Upon completion, the patient and PT discuss and evaluate the simulation and repeat the process, with modifications to increase realism and meaning, including a progression towards physically and psychologically realistic and sport-specific training exercises.

**Fig. 2 Fig2:**
[figure not shown]
Modulating complexity of the MOTIFS DMI to adapt to the needs and desires of the patient in question

The MOTIFS model is a clinically feasible training model with implications for both physical and psychological rehabilitation. The aim is to improve knee strength and postural control and re-learn activity-relevant movements that are simultaneously more meaningful and enjoyable for the patient.

##### MOTIFS intervention

Care-as-usual rehabilitation exercises with integrated DMI constitute the MOTIFS model, the premise of which is that aspects of DMI are integrated into commonly used knee rehabilitation movements, as prescribed by the treating PT. The research team (NC, SG, GN, RD, EA) lead a workshop in which a PT specializing in neuromuscular training (GN) and a sport psychologist specializing in DMI (NC) train the physical therapists to deliver the MOTIFS training model. The workshop consists of a 5-h session in which physical therapists in the experimental group receive theoretical and practical instruction in the proper methodology of the MOTIFS model. Detailed information, including a film and a manual, is provided to aid in the effective implementation of the intervention in the clinical setting. It is also ensured that relevant equipment is available to patients (i.e. balls or sticks). Additional support workshops are held throughout the intervention period.

Participating PTs that have been educated on the implementation of the MOTIFS model explain, individualize, and administer the intervention to participants during face-to-face rehabilitation training sessions either individually or in small groups. This is supplemented by information and three face-to-face support visits by the SC with the patient, together with the PT, in order to allow for discussion and questions regarding the proper utilization of the MOTIFS model during supervised and at-home training sessions. These visits ensure proper patient fidelity and also assess whether the physical therapists are correctly using the MOTIFS model. Participants are instructed to train using the principles of the MOTIFS model, in which PT-prescribed physical exercises with simultaneous DMI are performed based on the participant’s desired activity-specific situation. MOTIFS training is applied in relevant situations and allows for separation between activity-specific functional movements and other aspects of rehabilitation that the PT deems necessary such as warm-up, strength training, balance training, mobility exercises, and/or cool-down.

#### Outcome assessment

Physical and patient-reported outcomes are assessed at baseline and 12 weeks; patient-reported outcomes are assessed 12 months post-inclusion (Fig. 1). Prior to the testing occasion, self-report questionnaires are distributed using the REDCap electronic data capture tool [32], hosted by Lund University. Demographic data (age, gender, height, weight, treatment type, and injury history) and physical testing data (Table 3) are collected by an experienced test-leader either at the participants’ respective clinics or at the university lab according to a data collection form including testing procedures (further information is available in the data management plan, available at the ClinicalTrials.gov registration page: NCT03473821). Outcomes are assessed at 12 weeks post-inclusion to assess physical and psychological readiness when a PT would likely consider a return to activity testing, and at 12 months to assess long-term rehabilitation outcomes.

**Table 3 Tab3:** Outcomes assessment—description of types of outcome and the data used for analysis

Outcome		Type	Outcome data
Patient-reported outcomes	ACL-RSI^a^	12 item self-report scale (0–100 for each item)	0% (worst) to 100% (best) mean of summed total score
	KOOS	The normalized score for subscales: pain, symptoms, sports and recreational activity, activities of daily life, and quality of life	0 (worst) to 100 (best)
	PACES	18-item self-report scale (11 items reverse-scored)	18 (worst)–126 (best)
	PSS	10-item self-report scale	0 (best) to 40 (worst); 0–13 = low, 14–26 = moderate, 27–40 = high stress
	PEI	6-item self-report	0 (worst) to 12 (best)
	ROS	1-item self-report scale	Satisfied (3 or 2), mostly satisfied (1), or dissatisfied (0, −1, −2, or −3)
	RM	3-item self-report scale	0 (worst) to 10 (best); raw data presented
	TAS	3-item self-report scale (pre-injury, current, future)	1 (low activity)–10 (very high activity)
Physical testing	SH^a^	Number of completed hops	Change in the injured leg
	Hop test battery	SLHD-3 repetitions or until improvement <10cm; distance hopped (cm)	Change in the injured leg, change in the uninjured leg, LSI
		SH-number completed hops in 30 s	
	POEs	SLMS-5 repetitions; POEs assessed throughout the entire movement	Total POEs score
		SD-5 repetitions; POEs assessed on loading leg throughout entire movement until both feet are on the floor	
		FL-3 repetitions; POEs assessed on the front leg from landing until maximum flexion of the knee	
		SLHD-POEs assessed from landing until the knee is extended	
		SH-7 repetitions; POEs assessed during landing in 3 medial and 3 lateral jumps	
Adherence		Self-report questionnaire	Number and duration of training sessions
		Physical therapist report	Number of sessions attended
Adverse events		Self-report questionnaire	Number and type of adverse events, if any
Exploratory outcomes		Phenomenological interview	Coded interview data

*ACL-RSI* ACL Return to Sport after Injury Scale, *KOOS* Knee Injury and Osteoarthritis Outcome Score, *PACES* Physical Activity Enjoyment Scale, *PSS* Perceived Stress Scale, *PEI* patient enablement instrument, *ROS* rehabilitation outcome satisfaction, *RM* rehabilitation motivation, *TAS* Tegner Activity Scale, *SH* side hop, *SLHD* single-leg hop for distance, *LSI* Limb Symmetry Index, *POEs* postural orientation errors, *SLMS* single-leg mini squat, *SD* stair descending, *FL* forward lunge, *ADL* activities of daily life

^a^Main outcome

#### Main outcomes

This trial includes two main outcomes. Psychological readiness to return to sport is evaluated using the Swedish version of the ACL-Return to Sport after Injury scale (ACL-RSI), which includes an emotional response, confidence, and risk-appraisal when returning to sport after an ACL injury [33, 34]. Physical function is evaluated using the change in number of hops in the injured leg from baseline to 12 weeks for the side hop task.

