### Participants and randomization

Approximately 106 participants are recruited according to inclusion criteria (Table 1) from physical therapy clinics in Sweden. Physical therapists (PTs) fulfilling inclusion criteria (Table 1) from these clinics are included in the trial. The eligibility criteria for both PTs and participants allow for the recruitment of a sample of knee-injured people and their PTs representative of the population. To avoid contamination, participating clinics are block randomized by a third party using a random numbers generator and sealed opaque envelopes to either the experimental or CaU condition.

**Table 1 Tab1:** Participant and physical therapist inclusion and exclusion criteria

Participants	
Inclusion	Exclusion
- Men and women 16 years or older - Traumatic knee injury (e.g., ligament, meniscal, patellar, or chondral injury), with or without surgical intervention, and involving one or more knee structures - Currently undergoing physical therapist-supervised rehabilitation training - Have reached the stage in their rehabilitation which includes single-leg hop training, as well as a change of direction - Active before the injury in recreational or competitive physical activity, with a goal of returning to physical activity	- Any degenerative knee disorder (e.g., osteoarthritis), or other disease or disorder (e.g., spine disorder, neurological disease) overriding the traumatic knee injury - Reached end-stage rehabilitation (i.e., have undergone a return to physical activity evaluation by their physical therapist, or is estimated to return less than 12 weeks from potential inclusion date) - Do not understand the languages of interest (Scandinavian languages, English)

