### Statistical analyses

#### Sample size

Based on previous studies examining ACL-RSI [49] and side-hop function [50], a preliminary sample size was estimated, to be used in the first phase of this adaptive RCT, which resulted in *n*=106 participants. This included adjustments for potential cluster effects using a preliminary Intra-Cluster Correlation Coefficient (ICC). An approximation is required as comparable studies are unavailable to reliably perform a sample size estimation. This is necessary in this phase in order to evaluate whether an intervention effect is detectable and within practical limitations, which will thereafter inform more accurate sample-size estimations.

A new sample size will be calculated by a blinded third-party member of the data management committee using collected data from an interim analysis, therefore allowing for more accurate between-group differences in the main outcomes. Observed within- and between-cluster variance will also be calculated in order to more accurately estimate an Intra-Cluster Correlation Coefficient (ICC, denoted as *ρ*). This will be performed using the formula $$ \rho =\frac{s_b^2}{s_b^2+{s}_w^2} $$ [51] in order to adjust for the fact that different clinics are included in the trial (i.e., potential clustering effects). The adjusted sample size will therefore be calculated using the formula $$ \frac{n_ik\left(1-\rho \right)}{k-{n}_i\rho } $$ [52], along with an estimated 20% drop-out rate, in order to reach a power of 0.80, with significance set at *p*<0.025. As an estimated sample size has been calculated, the new sample size will only be adjusted up; that is, the number of participants included will not be less than *n*=106 required in the original sample-size estimation.

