#### Data analysis

The analysis will be done using the IBM SPSS statistical software package (IBM Corp., Armonk, New York, USA). Primary analyses of the entire sample will be done according to intention-to-treat principles. A dose-response analysis will be performed to determine effective adherence. Per-protocol analyses will be performed for those participants with at least 70% adherence (corresponding to two trainings per week), as a preliminary estimate of the effective number of training occasions. This is in order to eliminate cross-over and drop-out effects in the total sample, as well as to evaluate the training for those that have reached a pre-defined level of adherence deemed acceptable to have an effect. Sensitivity analyses will be performed to determine whether within-cluster correlations indicate potential effects due to being clustered, for example, by the clinic or by PT. Patient cross-over (i.e., patients changing clinics) is a low-risk possibility and will be recorded in case of occurrence. All outcome variables will be examined for normality using appropriate testing (e.g., Kolmogorov-Smirnov). Complete-case analyses are the primary analyses, and sensitivity analyses will be done depending on the number of missing values. Missing values are not expected to be extensive, and if less than 5% of data is missing, the whole data set will be analyzed along with a sensitivity analysis with appropriate imputed values. If between 5 and 40% of data is missing, appropriate multiple imputation methods will be used, which will be informed by blindly assessing results of the interim analysis, and a complete-case analysis will be done with appropriate sensitivity analyses. If over 40% is missing, a complete case analysis will be done with no sensitivity analysis.

Results will be analyzed using independent samples *t* tests to examine between-group differences of the change from baseline to a 12-week follow-up. Where appropriate, equivalent non-parametric Wilcoxon signed-rank testing will be used to compare between-group differences. The main analysis will focus on the two main outcomes, with secondary outcomes acting as support for these. Secondary outcomes therefore carry less weight and issues with potential error due to the number of evaluations will be discussed when results are presented.

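### The ACL-RSI main outcome is described for ACL injury only, yet all traumatic knee injuries are pooled in an unadjusted test; dilution is possible but not shown, and injury mix may differ between arms

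*Protocol article*

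**What the plan says.** **Outcome.** The Main outcomes section states "This trial includes two main outcomes": the ACL-RSI for psychological readiness, and the change in side hops on the injured leg. It describes the ACL-RSI as a scale "which includes an emotional response, confidence, and risk-appraisal when returning to sport after an ACL injury".

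**Population.** Table 1 admits "Traumatic knee injury (e.g., ligament, meniscal, patellar, or chondral injury), with or without surgical intervention, and involving one or more knee structures". An ACL injury is not required.

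**Analysis.** Under Data analysis, "Primary analyses of the entire sample will be done according to intention-to-treat principles", and "Results will be analyzed using independent samples *t* tests to examine between-group differences of the change from baseline to a 12-week follow-up". The test as stated has no term for injury type. The sensitivity analyses described there concern clustering by clinic or therapist, and missing data.

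**Allocation.** Under Participants and randomization, "participating clinics are block randomized by a third party using a random numbers generator and sealed opaque envelopes". No balancing by injury type is stated.

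**Data at hand.** The Outcome assessment section lists "Demographic data (age, gender, height, weight, treatment type, and injury history" among the items collected.

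**Disclosure.** The limitations in the Discussion cover blinding, what participants are told and the weak basis for the sample size. They do not mention the fit of the ACL-RSI to other injuries. The section on patient-reported outcomes does say that the satisfaction question is unvalidated and that the enjoyment scale is an unpublished translation. Both are secondary measures.

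**The concern.** The instrument is described for a narrower group than the one enrolled, and it carries half of the main hypothesis. Three things follow.

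- **Interpretation.** If the pooled ACL-RSI result is null, an ineffective intervention cannot be told from a scale that registers change poorly in part of the sample. If it is positive, the pooled estimate alone does not show how far it extends to people without ACL injury.
- **Adaptive decisions.** An ACL-RSI difference of at least 5 points is one of the interim continuation criteria, and interim data feed the new sample size. Any dilution would enter both.
- **Imbalance.** Clinics may see different kinds of knee injury. Because whole clinics are allocated, the proportion with ACL injury can differ between arms, and an unadjusted t test does not account for that.

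**Working it through.** **The plan's own figure.** The preliminary sample size is 106. The article says "Based on previous studies examining ACL-RSI [49] and side-hop function [50], a preliminary sample size was estimated" but gives no planning difference, standard deviation or preliminary ICC, so 106 cannot be rebuilt. As a reference point only: with no clustering, two-sided alpha 0.025 and 80% power, the number per arm is 2 × (2.2414 + 0.8416)² / d². For d = 0.60 this is 2 × 9.505 / 0.36 = 52.8, so 53 per arm and 106 in total before dropout, or 106 / 0.8 = 132.5, so 133 with 20% dropout. This neither confirms nor refutes 106.

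**Inputs for the dilution check.**
- Power 0.80, alpha 0.025 and 20% dropout: Sample size section. Sidedness is not stated; two-sided is assumed.
- f, the share without ACL injury: not given. 30% is used, with 10% and 50% as a range.
- r, the effect seen on the scale in non-ACL participants relative to ACL participants: not given. The values 1, 0.5 and 0 are used.

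**Formula.** The pooled effect is the ACL effect times m = (1 − f) + f × r. At 80% power the noncentrality is 2.2414 + 0.8416 = 3.083. Power after dilution is Φ(3.083 × m − 2.2414).

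**Results at f = 30%.**
- r = 1: m = 1; Φ(0.842) = 80%.
- r = 0.5: m = 0.85; 3.083 × 0.85 = 2.621; Φ(0.379) = 65%.
- r = 0: m = 0.70; 3.083 × 0.70 = 2.158; Φ(−0.083) = 47%.

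**Range over f.**

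| Non-ACL share | r = 1 | r = 0.5 | r = 0 |
|---|---|---|---|
| 10% | 80% | 75% | 70% |
| 30% | 80% | 65% | 47% |
| 50% | 80% | 53% | 24% |

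If 106 gave 80% power, the total that restores it is 106 / m². At f = 30% that is 106 / 0.7225 = 147 for r = 0.5 and 106 / 0.49 = 217 for r = 0.

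**Interim threshold.** For the pooled difference to reach 5 points at f = 30%, the ACL participants must differ by 5 / 0.85 = 5.9 points (r = 0.5) or 5 / 0.70 = 7.1 points (r = 0).

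**Imbalance.** Suppose mean change differs by δ between ACL and non-ACL participants whatever the treatment, and the ACL share differs by Δ between arms. The unadjusted difference then shifts by Δ × δ. Neither quantity is in the article, so no size can be given.

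**Precision of a breakdown.** With 106 × 0.8 ≈ 85 analysed, f = 30%, equal arms and no clustering, there are about 29.75 ACL and 12.75 non-ACL participants per arm. The 95% half-widths in SD units are 1.96 × √(2/29.75) = 0.51 and 1.96 × √(2/12.75) = 0.78. For the interaction the half-width is √(0.51² + 0.78²) ≈ 0.93.

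**The case against.** **The harm is not demonstrated.** Emotional response, confidence and risk appraisal are not specific to one ligament, and the article shows no item wording or validation data. If the scale works equally well in all knee injuries, nothing is lost. This stands, and it is why the point is limited to a possible dilution. A reader might infer that the trial is underpowered, or that the scale is invalid for part of the sample. The article supports neither.

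**Both arms use the same scale.** A reader might infer that the mismatch biases the comparison. By itself it does not. Only a difference in injury mix between arms could, and none is shown.

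**The sample size is re-estimated.** The new calculation uses interim data from the same mixed population and can only go up, so dilution would be partly picked up. This stands: the 65% and 47% apply before that step. It is not a full answer. The interim comparison is made at 25 per group, and 217 in total (about 109 per arm) would exceed the 100 per group that the plan treats as unrealistic and as a reason to modify the method.

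**Pooling is deliberate, and subgroup analyses belong in an analysis plan.** The trial is pragmatic and aims for a representative sample, so the average effect is a legitimate target. An unlisted subgroup analysis is no defect here. What remains is what the article itself fixes: this instrument, this eligibility and an unadjusted main test, with no support for the combination and no mention of it as a limitation.

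**Conclusion.** The mismatch is in the text: a main outcome described for ACL injury, enrolment without an ACL requirement, and one unadjusted pooled test. The consequence is a risk to interpretation, not a numerical error. At an assumed 30% non-ACL share, power lies between 80% and about 47% according to how the scale responds in those participants, with about 65% at half response. The extremes rest on assumptions that the article neither supports nor excludes, and the calculation ignores clustering and precedes any re-estimation. Possible imbalance in injury mix between arms is a separate matter and follows from randomizing clinics. It can be reduced in the analysis at almost no cost.

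**What to change.** 1. In the ACL-RSI main analysis, replace the unadjusted t test with a model of change that includes ACL injury (yes/no) as a covariate. Count a participant as yes if the ACL is among the injured structures. The information should be available from the eligibility check and the injury history; confirm that the form records the structures injured. This addresses imbalance. It still estimates one averaged effect, so it does not undo dilution.
2. Pre-specify, as a supportive analysis, the ACL-RSI treatment estimate with confidence interval separately for ACL and non-ACL participants, with the interaction shown. Set no pass/fail rule for agreement: the intervals will be too wide for one, and comparing the ACL subset with the full sample would compare overlapping groups.
3. Add to the limitations that the scale is described for ACL injury. Either cite support for its use in other knee injuries or word the readiness conclusion for those injuries accordingly.

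The cost is a change of analysis wording, one supportive analysis and a sentence of limitation, with no new visit, instrument or participant. The downside is that the subgroup estimates will be imprecise, most of all in the non-ACL group.
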